#### 2.6.2. Cognitive Assessments

Modified versions of the N-Back and Erikson Flanker tasks are employed to assess the inhibitory control and working memory as two components of executive function. Both tasks are administered with E-Prime 3.0 (Psychological Software Tools, Pittsburg, PA, USA). Each task consists of a practice block and two test blocks. 

Visual stimuli in the N-back test are capital letters presented one at a time. For each letter, participants are instructed to indicate whether the actual letter matches the previous letter in the series by pressing a button with the left or right index finger. The adjusted hit rate and reaction time are calculated as outcomes. The results of a study published by Kearney-Ramos and colleagues [32] support the use of the n-back test as a viable and valid measure of working memory.

Visual stimuli in the Eriksen Flanker task are five arrows presented in a congruent or incongruent sequence. In congruent trials, the central target arrow faces in the opposite direction of the flanking arrows, whereas all arrows point in the same direction in incongruent trials. Participants are instructed to indicate the direction of the central arrow by pressing a button with the left or right index finger. Reaction time (on response-correct trials) and accuracy are calculated as outcomes [33].

The mini-mental state examination (MMSE) is employed at baseline to rule out cognitive impairment. The MMSE assesses orientation, memory, attention, calculating, writing and speech and showed good reliability (r = 0.89) [34].

#### 2.6.3. Cardiovascular Assessments

All cardiovascular assessments, except the retinal vessel analysis, are performed by a medical doctor or by qualified personnel under a doctor’s supervision.

To evaluate the aerobic capacity of the participants, a spiroergometric test on a cycle ergometer (Ergoline, Bitz, Germany) with maximal oxygen consumption (VO2max) (Cortex Metamax, Leipzig, Germany) and electrocardiogram (ECG) (Amedtec, Aue, Germany) measurements are conducted. The test is started at 25 W with an increment of 25 W every three minutes until subjective exhaustion is reported. Thereby, common exhaustion criteria were applied [35]. At the end of each level, heart rate and blood pressure are measured and a capillary blood sample is drawn from the ear lobe to measure and evaluate lactate concentrations. Participants are asked to state their perceived exertion on the BORG scale after every level [36]. For spiroergometric assessment, the peak and relative peak oxygen consumption related to body weight (VO2peak) and the maximum power (Wpeak) are assessed.

Pulse wave velocity (cfPWV) is assessed as a measure of arterial stiffness using an oscillometric device with integrated ARCSolver® software (Mobil-O-Graph® Monitor, I.E.M. GmbH, Stolberg, Germany). The measurements of arterial stiffness and central hemodynamics using the oscillometric method stand in good agreement with the conventional tonometric method [37]. All measurements are performed in a fasting state. Patients are required to refrain from physical exercise, eating as well as drinking alcohol or caffeine 12 h prior to measurements. The blood pressure cuff is placed on the left upper arm while the patient is lying in a resting supine position. After 10 minutes of rest, three measurements are performed with two-minute intervals in between. From the measurements, central blood pressure, the augmentation index at heart rate 75/min (AIx@75) as well as cfPWV are extracted. cfPWV is automatically calculated from the pulse wave data and reflects the assessment of central, aortic arterial stiffness. After data readout, every measurement is reviewed for erroneous values. The mean and standard deviation of three valid measurements are calculated. 

Furthermore, heart rates, heart rhythm and heart rate variability are documented using a 24 h electrocardiogram (ECG) (Langzeit-EKG, Amedtec, Aue, Germany). Blood pressure is documented over 24 hours every 30 minutes during the day and every 60 minutes during the night using a standard cuff (Mobil-O-Graph®, IEM, Stolberg, Germany).

A non-invasive retinal vessel analysis is conducted to measure retinal vessel diameters as microvascular biomarkers of cardiovascular risk using a fundus camera and a semi-automated software system (SCA-T, Imedos Systems UG, Jena, Germany). Three images of the right eye are taken at a 45° angle with the optic nerve at center. Arterioles and venules at a distance of 0.5–1 times the diameter of the optic nerve are semi-automatically analyzed (Vellelmap 2, Visualis, Imedos Systems UG, Jena, Germany). The high reliability of this method has been shown [38,39]. 

Echocardiography is performed by an experienced echocardiographer using the Vivid iq with a M5Sc 1.5-4.6 transducer (GE Healthcare Systems, Boston, MA, USA, 2018). The participant lies in a semi-supine resting position. Images are taken based on the recommendations of the American Society of Echocardiography (ASE) while the participant holds his breath [40]. Conventional echocardiography includes standard measurements of cardiac dimensions, contractility and diastolic function. Speckle tracking images for calculation of myocardial strain are recorded in apical three-chamber, two-chamber and four-chamber views for longitudinal values and in the parasternal short-axis at the level of papillary muscles for circumferential and radial values. Analysis of all images is conducted offline using EchoPac-Software (Version 202, GE Healthcare, Boston, MA, USA, 2018).

#### 2.6.4. Psychosocial Assessments

Participants complete various questionnaires in written form. 

Depressive symptoms are assessed using the short “Centre for Epidemiological Studies Depression Scale” (CES-D) with 15 items, containing depression related cognitive, emotional, motivational, somatic and behavioral aspects [41]. The validity of the CES-D has been shown [42].

The German version of the “Perceived Stress Scale” (PSS) with ten items is used to inquire the perceived stress of the past months [43]. Its validity and reliability have been shown [44] and the scale is commonly used with older adults [45].

To quantify sleep complaints, participants answer the “Insomnia Severity Index” (ISI) [46]. A positive evaluation of its reliability (Cronbach α = 0.9) is published [47] and it is often used with older adults [48].

A short German version of the “World Health Organizations Quality of Life Questionnaire” (WHOQOL BREF) is also applied in order to assess global measures of quality of life [49]. Internal consistency measures were high (Cronbach’s alpha = 0.9) [50].

The fear of falling is recorded using the “German Version of the Falls Efficacy Scale—International Version” (FES-I) [51], which is a valid and reliable scale [52].

### 2.7. Interim Assessment

The following measurements are only applied at the interim assessment: Maximal strength assessment of leg extension, leg curl and handgrip; gait speed (in single-, dual-task- and triple-task conditions); balance (static and perturbed); psychosocial questionnaires (CES-D, PSS, ISI, WHOQOL).

### 2.8. Intervention

The first training session takes place immediately after group allocation. Participants train in three separate groups with a maximum of 13 participants in each group. Two trained study assistants supervise all sessions. Each of the training groups train twice a week for one year with a two-week Christmas break. Training sessions are held at gyms, located at the campus of the German Sport University Cologne. The gyms are equipped with regular basic equipment (e.g., mats, cones, ropes, hoops). The sessions last for 60 min in total and consist of a diverse 10 min agility-specific warm-up, followed by a 45 min agility training and a 5 min cool-down. Training is accompanied by music in line with the preferences of the participants. The warm-up either consists of a series of instructed exercises, dance-like routines or exercises incorporating balls. The agility training part is divided into three to four stations that the participants attend in pairs or in small groups. The load duration is one minute, followed by one minute of rest with four to five repetitions at each station. In the last third of the one-year intervention period, more complex parkour settings are installed. The individual load duration exceeds one minute and the time for rest is longer. As briefly described in the introduction, agility training includes four components: start-stop, change-of-direction, balance and strength. In order to progressively design training sessions, the one-year intervention period is divided into three thirds. During the first third, two of the four agility components are part of each training session, alternating every second session. In the second third, three of four components are combined in every session and then, only in the last third, all agility components are simultaneously integrated in each session. The complexity of the training sessions is progressively increased by changing the physical, perceptual and/or cognitive loads of the exercises. The training design and progression are displayed in Figure 2. Participants are always pointed to potential hazards during the exercises (e.g., stumbling over mats, slipping on a cone). They are taught to give each other assistance, e.g., during balancing exercises. Any adjustment of the original training protocol as well as adherence for every session is documented in detail by the coach. For each session, participants are asked to state their overall rate of perceived exertion (BORG scale) immediately after the end of the session. Additionally, in each session, three to four randomly chosen participants wear heart rate sensors (polar, H7, Buettelborn, Germany) to exemplarily capture heart rates during the training. A participant does not continue the allocated intervention if he or she requests it or suffers pain or an injury. Adverse events are recorded and potential sources will be discussed and eliminated if necessary.

### 2.9. Sample Size Estimation and Statistical Procedures

A sample size estimation was conducted with G*Power (Version 3.1, Heinrich Heine University, Duesseldorf, Germany). 68 participants (34 per group) are needed for statistical analysis, assuming moderate effects (f = 0.2) for training-induced changes in the primary outcomes (statistical power 90%, two-sided significance level α=.05). Expecting a realistic dropout rate of about 25%, a total of 85 participants were initially recruited.

Data entry will be double-checked and data ranges will be controlled for plausibility. Two researchers ([name]) will do data management and analysis. Independently conducted two-factorial repeated measured analyses of co-variance (rANOVA), with the respective endpoint as a baseline measure serving as the covariate [53], will be computed as primary analysis to assess the time course of adaptations between groups (factor 1: control group vs. intervention group; factor 2: time point of measurement; baseline, interim, post). The rANOVA interaction term between both factors is the main term of interest. Together with 90% confidence intervals, change scores from T1 to T3 and from T1 to T2 and T2 to T3 are calculated to arrive at an estimate of the size of the observed effects. The intention-to-treat analysis will be computed. The intention-to-treat analysis will be compared to as-treated analysis. Potential differences will be discussed.

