In conclusion, it seems promising that agility training can serve as a feasible and time-efficient way to address a variety of health-related aspects relevant for the aging process. Numerous objective measures of neuromuscular, cardiovascular, cognitive and psychosocial origin can be challenged twice a week without excessive training volumes (which are not likely achievable by older adults). To our knowledge, no randomized controlled long-term intervention has applied the agility framework yet. Based on the above-mentioned rationales, we aim at introducing the protocol of an ongoing randomized controlled trial, investigating the effects of a one-year agility training intervention on neuromuscular performance, cardiovascular and cognitive functioning, as well as relevant psychosocial health outcomes in community-dwelling, healthy older adults. We specifically hypothesize that the agility training approach induces notable improvements in all physical performance measures (strength, balance, motor performance, aerobic capacity) after the one-year intervention period when compared to an inactive control group with at least moderate effect sizes that are comparable to other traditional training regimens. Secondly, we assume that those training effects will already be visible after six months of training with a further steady increase until the end of the one-year period. This study protocol was designed to contribute to a preventive multimodal training concept that can improve physical, cognitive and psychosocial health outcomes relevant to warrant healthy aging in an integrative and time-efficient way.

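### The 90% power claimed for a moderate effect holds, on the simplest calculation that gives 68, for a 0.8 SD difference in change, which is conventionally large

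*Protocol article*

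**What the plan says.** Section 2.9 of the protocol article reports: "A sample size estimation was conducted with G*Power (Version 3.1"). It gives the result as "68 participants (34 per group) are needed for statistical analysis, assuming moderate effects (f = 0.2) for training-induced changes in the primary outcomes", with "statistical power 90%, two-sided significance level α=.05". It does not give the number of measurements, the correlation between them or the sphericity value, and it does not express f as a difference between groups.

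The same section sets out a baseline-adjusted repeated-measures analysis with "factor 2: time point of measurement; baseline, interim, post", and says: "The rANOVA interaction term between both factors is the main term of interest".

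The hypothesis in the Introduction uses the same adjective. Improvements are expected "when compared to an inactive control group with at least moderate effect sizes that are comparable to other traditional training regimens". No number is attached to it there.

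**The concern.** Cohen's f has no fixed meaning as a difference between two groups until the design is known. In a plain two-group comparison at one time, f = d/2, so f = 0.2 is 0.4 SD, and 90% power would take 266 participants. A total of 68 is possible only because f here belongs to a repeated-measures interaction, where the same value stands for a much larger difference in change.

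A reader of Section 2.9 cannot see this. The reader is told that the trial has 90% power for moderate effects, and the Introduction says that at least moderate effects are what the trial tests. If the 90% applies to a large effect, a non-significant interaction on a primary endpoint could be taken as good evidence against a moderate benefit when it is not.

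**Working it through.** **Inputs from Section 2.9:** f = 0.2, alpha 0.05 two-sided, power 90%, two groups of 34, group-by-time interaction as the tested term.

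**Inputs assumed because they are not stated:** number of time points m, correlation rho, sphericity epsilon.

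**1. Reproduce 68.** For the G*Power within-between interaction with k = 2 groups:

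- lambda = f² × N × m × epsilon / (1 − rho)
- df1 = (k − 1)(m − 1) × epsilon; df2 = (N − k)(m − 1) × epsilon

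With m = 2, rho = 0.5, epsilon = 1 and N = 68: lambda = 0.04 × 68 × 2 / 0.5 = 10.88, df = 1 and 66, power 0.9015. N = 66 falls short of 90%, so 68 is the smallest even N.

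**2. Other routes at f = 0.2.**

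| Time points | rho | epsilon | N |
|---|---|---|---|
| 2 | 0.5 | 1 | 68 |
| 2 | 0.3 | 1 | 94 |
| 2 | 0.7 | 1 | 42 |
| 3 | 0.5 | 1 | 56 |
| 3 | 0.37 to 0.38 | 1 | 68 |
| 3 | 0.5 | 0.75 | 68 |

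Two time points with rho 0.5 is the simplest route to 68, but not the only one. The three time points of the analysis model, with rho 0.5 and sphericity, give 56.

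**3. Translate f = 0.2 for two time points.** Let the groups differ by D in mean change. The four interaction effects are each ±D/4, so f = D/(4 SD) and D = 4 × 0.2 × SD = 0.8 SD. The SD of a change score is SD × √(2(1 − rho)), which at rho 0.5 equals the outcome SD. As a check, a two-sample t test with d = 0.8 and 34 per group has power 0.9015, the same as in step 1.

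With baseline as covariate the residual SD is SD × √(1 − rho²) = 0.866 SD at rho 0.5. The difference with 90% power is then about 0.8 × 0.866 = 0.69 SD.

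**4. Translate f = 0.2 for three time points.** The interaction effects are half the centred profile of D.

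- Linear profile (0, ½, 1): f = 0.204 × D/SD, so D = 0.2/0.204 = 0.98 SD.
- Step profile (0, 1, 1) or (0, 0, 1): f = 0.236 × D/SD, so D = 0.2/0.236 = 0.85 SD.

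Both exceed 0.8 SD. With rho 0.37, interaction-test power for D = 0.5 SD is about 35% to 45%.

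**5. Power for 0.5 SD with 68 analysed.** The standardised difference is 0.5/√(2(1 − rho)) for change scores and 0.5/√(1 − rho²) for ANCOVA (noncentral t; 66 and 65 df).

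| rho | Change score | ANCOVA |
|---|---|---|
| 0.5 | 53% | 65% |
| 0.6 | 62% | 72% |
| 0.7 | 75% | 81% |
| 0.8 | 89% | 92% |

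If all 79 randomized participants were analysed, the rho 0.5 figures would be about 59% and 72%. At rho 0.5, 90% power for 0.5 SD would take about 172 (change score) or 130 (ANCOVA).

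**The case against.** **The inputs are inferred.** This stands. An article need not list every software setting, and their absence is not the fault raised here. The inference does not drive the conclusion, because the three-time-point routes to 68 that were checked imply a still larger difference.

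**Moderate need not mean 0.5 SD.** This stands too. The article attaches the word only to f = 0.2, and nowhere promises 90% power for 0.5 SD. What remains is that the label, left untranslated, covers a difference of about 0.8 SD. At 0.6 SD and correlation 0.5, power is still only 68% (change score) or 80% (ANCOVA).

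**The real correlation may be well above 0.5.** Sections 2.5 and its test descriptions cite reliabilities from 0.75 to 0.94 for the primary endpoints. At correlation 0.8 the trial would have close to 90% power for 0.5 SD. But these are reliabilities, not correlations over one year, and Section 2.9 does not say that they were used. With two time points and correlation 0.7, f = 0.2 would have given 42, not 68.

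**Stronger readings that a reader might infer, and that the document does not support:**

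- *That 68 is miscalculated.* It reproduces exactly on its own metric.
- *That three planned time points make 68 too small.* At correlation 0.5 with sphericity they would lower N to 56. Two time points is also a natural basis, since Section 2.3 places endpoint collection at pre- and post-testing and the interim list in Section 2.7 omits the ACE, a primary endpoint.
- *That the trial will have only 53% to 65% power for a moderate effect.* That holds at correlation 0.5; the true correlation is unknown.

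Section 2.9 also plans change scores with 90% confidence intervals, which lessens the risk of over-reading a null result but does not correct the power statement.

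**Conclusion.** The concern holds as a mislabelled power statement. On the simplest reconstruction, 90% power applies to a between-group difference in change of 0.8 SD, or about 0.69 SD with baseline adjustment; by the usual convention 0.8 SD is a large effect. For 0.5 SD with 68 analysed, power runs from 53% to 89% (change score) or 65% to 92% (ANCOVA) as the correlation goes from 0.5 to 0.8.

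This rests on three assumptions: the two-time-point, correlation 0.5 reconstruction; 0.5 SD as the benchmark for moderate; and the stated range of correlations. The direction is robust to the first. The size of the shortfall depends on the other two. The point matters because the same adjective defines the hypothesis that the trial sets out to test.

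**What to change.** Keep N; recruitment and randomization are complete. In Section 2.9:

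1. State the inputs actually used (time points, correlation, sphericity). The values inferred here should not be adopted unless they are the ones that were used.
2. Give the detectable difference in SD units: 0.8 SD in change if two time points and correlation 0.5 were used, with about 0.69 SD for the baseline-adjusted comparison.
3. Drop the word moderate or qualify it.
4. Add the power for 0.5 SD at correlations from 0.5 to 0.8.
5. State that a non-significant interaction does not exclude a moderate effect, and that null results will be read from the planned confidence intervals.

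The cost is a few sentences. The trial's stated sensitivity will look less favourable; its design and analysis do not change.

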## Abstract

Exercise training effectively mitigates aging-induced health and fitness impairments. Traditional training recommendations for the elderly focus separately on relevant physiological fitness domains, such as balance, flexibility, strength and endurance. Thus, a more holistic and functional training framework is needed. The proposed agility training concept integratively tackles spatial orientation, stop and go, balance and strength. The presented protocol aims at introducing a two-armed, one-year randomized controlled trial, evaluating the effects of this concept on neuromuscular, cardiovascular, cognitive and psychosocial health outcomes in healthy older adults. Eighty-five participants were enrolled in this ongoing trial. Seventy-nine participants completed baseline testing and were block-randomized to the agility training group or the inactive control group. All participants undergo pre- and post-testing with interim assessment after six months. The intervention group currently receives supervised, group-based agility training twice a week over one year, with progressively demanding perceptual, cognitive and physical exercises. Knee extension strength, reactive balance, dual task gait speed and the Agility Challenge for the Elderly (ACE) serve as primary endpoints and neuromuscular, cognitive, cardiovascular, and psychosocial meassures serve as surrogate secondary outcomes. Our protocol promotes a comprehensive exercise training concept for older adults, that might facilitate stakeholders in health and exercise to stimulate relevant health outcomes without relying on excessively time-consuming physical activity recommendations.

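### The dropout allowance is miscalculated: 85 participants cover 20% loss, not 25%, so 68 analysable and 90% power are not reached at the planned rate

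*Protocol article*

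**What the plan says.** Section 2.9 of the protocol article gives the analysis requirement as "68 participants (34 per group) are needed for statistical analysis". The stated inputs are an effect size, "assuming moderate effects (f = 0.2) for training-induced changes in the primary outcomes", and error rates, "statistical power 90%, two-sided significance level α=.05". The allowance for loss follows: "Expecting a realistic dropout rate of about 25%, a total of 85 participants were initially recruited".

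The Abstract gives the counts actually reached: "Eighty-five participants were enrolled in this ongoing trial", and then "Seventy-nine participants completed baseline testing and were block-randomized to the agility training group or the inactive control group".

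Section 2.9 does not mention the 79. Nowhere does the article revise the 68, the 25% or the 90% in light of it, and it describes no replacement of participants who are lost. It does not say whether the 25% is counted from enrolment or from randomisation.

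**The concern.** Three figures in section 2.9 (68 needed, about 25% lost, 85 recruited) do not fit together. The 85 comes from adding a quarter of 68 to 68, but a dropout rate is a share of those who enter, not of those who remain. The six people who left between enrolment and randomisation narrow the margin further.

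What is at stake is how the results are read. Anyone interpreting a null result on a primary endpoint will rely on the 90% figure. If dropout runs at the rate the article itself expects, fewer than 68 are available and power is somewhat lower than stated.

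**Working it through.** **Inputs from the article.** Section 2.9: 68 analysable (34 per group), f = 0.2, α = 0.05, power 90%, dropout d = 25%, 85 recruited, group-by-time interaction as the term of interest. Abstract: 85 enrolled, 79 randomised.

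**Inputs assumed.** The number of measurements m and the correlation r between them used for the sample size are not stated. I took values that reproduce 68, with sphericity (ε = 1).

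**Step 1: reproduce the 68.** Repeated-measures within-between interaction, two groups, noncentral F with λ = f²·N·m/(1 − r), df₁ = m − 1, df₂ = (N − 2)(m − 1).
- m = 2, r = 0.5: λ = 0.04 × 68 × 2/0.5 = 10.88; power 90.2%. At N = 66 it is 89.3%, so 68 is the smallest even N reaching 90%.
- m = 3, r = 0.375: λ = 0.04 × 68 × 3/0.625 = 13.06; power 90.3%. At N = 66 it is 89.3%, so this also gives 68.

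The stated 68 is therefore reproducible, and the fault lies only in the step after it.

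**Step 2: reproduce the 85.**
- n(1 + d) = 68 × 1.25 = 85, the article's figure.
- n/(1 − d) = 68/0.75 = 90.67, so 91, or 92 for equal groups.
- The rate for which 85 is right: 1 − 68/85 = 20%.

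**Step 3: what remains at 25% dropout.**
- Base 85 enrolled: 85 × 0.75 = 63.75, about 64. The 6 already gone count towards the loss, so a further 79 − 64 = 15 would be lost after randomisation.
- Base 79 randomised: 79 × 0.75 = 59.25, about 59.
- Loss that still leaves 68 of 79: 79 − 68 = 11, and 11/79 = 13.9%.

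**Step 4: power at those numbers.**

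| Analysable N | m = 2, r = 0.5 | m = 3, r = 0.375 |
|---|---|---|
| 68 | 90.2% | 90.3% |
| 64 | 88.3% | 88.3% |
| 59 | 85.6% | 85.4% |

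The two settings agree closely. From the stated 90%, the shortfall is about 1.7 points at 64 and about 4.5 points at 59.

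**Sensitivity.** With m = 3 and r = 0.5, power at 59 is 92.4%. That setting needs only 56 participants, so it cannot be the source of the stated 68.

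**The case against.** The inflation step itself has no good defence. Calling the rate approximate does not rescue it, because 85 matches 20% and not 25%. The case on the other side concerns how much follows from the error, and most of that case stands.

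- **The base of the rate.** Section 2.9 attaches the 25% to the 85 recruited, so the six lost before randomisation can be read as part of it, leaving about 64. Taking a further 25% from 79 means 6 + 20 = 26 losses out of 85, or 30.6%. The figure of 59 is therefore one reading and cannot be presented alone. The wording settles neither, so the range 59–64 is the honest statement.
- **Unstated inputs.** The power values rest on m and r fitted to return 68. They are assumptions, not the article's own inputs.
- **Completers and the analysed set.** The article plans an intention-to-treat analysis, so treating the analysed number as those who do not drop out is also an assumption. It is the one section 2.9 makes when it adds a dropout allowance to the number needed for analysis.
- **The counts are disclosed.** The Abstract reports both 85 and 79, and no passage calls 85 the number randomised. What is missing is the link to the sample size.

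A reader might infer two stronger things. One is that the trial has already failed to deliver 68 participants and 90% power. The documents do not support that: the trial is ongoing, final attrition is not reported, and 68 remains reachable. The other is that power is far lower once significance is split across the four primary endpoints. Section 2.9 specifies no such adjustment, and a drop from that source would come mainly from the smaller α and not from the dropout arithmetic.

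**Conclusion.** The dropout inflation is wrong as written, on the article's figures alone and with no outside assumption: 25% loss calls for 91 participants, not 85. At the planned rate neither possible base leaves 68.

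The effect on power is small. The multiplication error by itself, on the enrolment base, costs about 2 points. If the full 25% is lost after randomisation, the cost is about 4.5 points, and most of it comes from starting at 79. These power figures hold for the m and r that reproduce 68, and only if the planned dropout occurs. The point is certain as arithmetic and modest in consequence; it does not call the design or the analysis into question.

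**What to change.** Reword the sample-size paragraph in section 2.9 so that it:

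- states that 85 were enrolled and 79 randomised;
- says whether the 25% is counted from enrolment or from randomisation;
- corrects the inflation to n/(1 − d), giving 91 (92 for equal groups) for 68 analysable at 25%;
- reports the expected analysable number, about 64 or about 59 according to the base, with power of about 88% or 85–86%, and names the number of measurements and the correlation used;
- notes that 68 is kept only if no more than 11 of the 79 (13.9%) are lost.

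The cost is a change of wording and a slightly less favourable power statement. No further recruitment and no change to the design or analysis is needed.
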